### Stage 5: Refinement

Stage 5 is the *refinement* phase that involves modification of the behavioural intervention based on the outcome measures, the feedback from the participants, as well as input from the Patient Advisory Committee. The goal of this stage is to prepare for and plan a future RCT to definitively evaluate the efficacy of the intervention based on the CF findings.

Table 4 provides a graphical timeline of the proposed study.

**Table 4 T4:** Study timeline.

Study period							
	Stage 1	Stage 2	Stage 3			Stage 4	Stage 5
Study phases	Development	Needs Assessment	Pre-intervention	Intervention	Post-intervention	Analysis & Dissemination	Refinement
Timeline	6 months	12 months	12 months	3 months	3 months
Development of intervention	X						
Preparation of facilitator manual	X						
Recruitment for Stage 2		X					
Enrolment for needs assessment survey		X					
Informed consent for survey		X					
Survey administration		X					
Survey data analysis		X					
Intervention modification		X					
Facilitator manual modification		X					
Training of occupational therapist			X				
Recruitment for Stage 3			X				
Eligibility screening			X				
Enrolment for intervention			X				
Informed consent for intervention			X				
Outcome measures							
PASAT			X		X		
PVT			X		X		
MFIS			X		X		
FSMC			X		X		
FSIQ-RMS			X		X		
BICAMS			X		X		
Phonemic fluency			X		X		
Semantic fluency			X		X		
HADS			X		X		
PHQ-9			X		X		
GAD-7			X		X		
DASS			X		X		
MSQOL-54			X		X		
PSQI			X		X		
Actigraph			X		X		
Structured interview			X		X		
Biomarkers			X		X		
Intervention sessions 1 through 8				X			
Facilitator SOAP notes				X			
Feasibility outcomes					X		
Completion rate of assessments					X		
Attendance at intervention sessions					X		
Homework adherence					X		
Attrition					X		
Facilitator SOAP notes completion					X		
Data analysis						X	
Knowledge translation						X	
Refinement							X
Future RCT planning							X

ActiGraph, ActiGraph Free-living activity accelerometer; BICAMS, Brief International Cognitive Assessment for Multiple Sclerosis; DASS, Depression Anxiety and Stress Scale; FSIQ-RMS, Fatigue Symptoms and Impacts Questionnaire-Relapsing MS; FSMC, Fatigue Scale for Motor and Cognitive Functions; HADS, Hospital Anxiety and Depression Scale; MFIS, Modified Fatigue Impact Scale; MSQOL-54, Multiple Sclerosis Quality of Life; PASAT, Paced Auditory Serial Addition Test; PHQ-9, Patient Health Questionnaire-9; PSQI, Pittsburgh Sleep Quality Index; PVT, Psychomotor Vigilance Task.

## Discussion

There is a recognized need for behavioural interventions targeting the improvement of CF given the negative implications for quality of life (24, 25) in approximately half of PwMS (32). Few interventions exist to date, with pharmacological approaches being unsuccessful (57), and procedural interventions being inaccessible to most PwMS (56). Our own work has demonstrated the promise of behavioural interventions (60) and that there are multiple contributing factors to CF that must be considered when designing such an intervention (38). The proposed pilot study addresses questions of *feasibility*, as well as a specific design feature where we test the *efficacy* of the intervention on a smaller scale in preparation for a future RCT (62).

Our group has conducted numerous studies before and thus do not anticipate any difficulties recruiting participants for either the Needs Assessment or Intervention components. We anticipate that recruiting individuals interested in the CF intervention will not be challenging given that this is an issue that affects approximately half of all individuals with MS (74). However, the process of screening interested individuals is likely to take the most time at this stage given that not all those expressing interest will meet eligibility criteria, particularly as it relates to objectively measured CF. This will require that a research assistant be present at MS Clinics so that screening can occur as soon as potential participants are identified. A graduate student (TI) will be assigned to this task given that the work will form part of the student's dissertation. As such, this is not expected to lead to any significant barriers.

An additional advantage of this study is that we are able to use technology to conduct both the needs assessment (i.e., internet-delivered survey) and intervention (i.e., internet accessible videoconference software) components. This limits face-to-face contact; a feature of this research that has become more necessary in the context of a global pandemic. While there is the possibility that a resurgence of COVID-19 could limit our ability to bring in participants for the pre- and post-intervention assessment sessions, this portion of the study is scheduled for 1 year in the future. As full lockdowns become less common, and hospitals are now better equipped to provide appropriate PPE and accommodations (e.g., use of a plexiglass screens, etc.), we do not anticipate that increased COVID-19 in the community will cause any significant study-related delays.

A further strength of this project is the inclusion of a needs assessment survey to ensure that the needs of PwMS are considered. Such a survey allows PwMS to identify the particular factors that they feel are important regarding their own CF and informs the development and refinement of the intervention. By taking into account the concerns identified by PwMS, we can be sure that the intervention will be tailored to meet their needs.

A potential limitation of any computer-based delivery model is that they have the potential to limit accessibility for those who are not confident in their technological skills or do not have access to the required hardware. However, the platforms we have chosen can both be accessed by smartphones. Although less ideal in terms of format, most individuals have access to smartphones and thus accessibility is not expected to be a barrier for participants.

The multidimensional nature of the intervention has both strengths and perceived limitations. By addressing multiple underlying components contributing to CF, the intervention can be tailored to meet the needs of each individual. This strength allows the intervention to address multiple factors that potentially contribute to CF in any given individual. While some might suggest that a multidimensional intervention does not easily allow for the identification of the most efficacious component, it is important to acknowledge that CF itself is a multidimensional symptom and what proves to be most efficacious for one individual may differ for another. While one person may find that increasing their physical activity improves their CF, another may find that addressing their mood concerns is of more benefit. So too might the factors contributing to CF in one individual change over time, with contextual factors being of more importance in 1 week and mood factors being more contributory in the next. The multidimensional nature of the intervention allows for the required flexibility to address these changing needs both between and within individuals.

We anticipate several outcomes from this project. First, we expect that the modifications identified by the needs assessment will be easily implementable into the planned intervention and associated facilitator manual. During the initial development in Stage 1 the intervention will be designed with these things already in mind. It is expected that each of the areas included in the needs assessment will be indicated as disruptive and currently unaddressed by at least some individuals. We anticipate that respondents will identify several areas of unmet need, particularly as they relate to treatments for fatigue, mood, and cognitive challenges. Our own group has identified a significant gap between the research progress in these areas and the services available to address these issues in standard clinical practice (75). While exercise interventions may be more readily available in the community at large, there continue to be environmental barriers to accessibility (76–78). The current intervention will be designed to address each of these components (i.e., body, mood, mind, context), highlighting once again, the flexibility of such an intervention. Second, we anticipate that at least 75% of the individuals enrolled in the intervention will complete 6/8 sessions (i.e., be successful completers). While attrition is anticipated in any intervention study, past studies have demonstrated that having at least 12 completers is sufficient to yield the necessary outcomes in a pilot study (68). Third, we anticipate that those completing the intervention will demonstrate an improvement in CF as measured by a positive and statistically significant change documented from baseline assessments. Fourth, taken together, the needs assessment and intervention are expected to inform the development of a future definitive RCT. If such an RCT were to be successful, then further RCTs to compare the efficacy of the behavioural intervention to procedural interventions (i.e., tDCS) and pharmacological interventions could be pursued.

The ultimate goal of this multi-staged project is to ensure that those with MS have access to effective interventions in real-world settings to improve the quality of their lives and enhance their ability to participate in cognitively demanding activities that they enjoy.

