### Stage 3: Implementation of intervention

Stage 3 is the *implementation* phase and will begin with the training of an occupational therapist who will administer the manualized intervention. This individual will be trained by the Principal Investigator and/or Co-Principal Investigators. Any issues arising from this training will be identified and subsequent training will be modified accordingly. Given the additional mood component in this study, there is the potential for the identification of individuals with serious mental health concerns. As such, a psychologist (LW and/or a consulting Clinical Psychologist) will be available should the intervention of a mental health professional be required throughout the project. With respect to participants, we will recruit a sample of 20 individuals with MS who meet the inclusion criteria from the Ottawa Hospital MS Clinic. The sample size was selected so that we can ensure that we have 15 individuals in the final sample (allowing for 25% attrition). This number was chosen given that previous research has suggested a minimum sample size of 12 to 15 is sufficient to determine feasibility of pilot studies in MS (68, 69). The primary inclusion criteria is that participants exhibit evidence of objective CF on the PASAT as defined by established normative data using ≥1.5 standard deviations below the mean (36). Inclusion criteria also include: (a) English-speaking; (b) ages 18–65 years; (c) EDSS <6.0; (d) relapse and steroid free in the past 30 days; (e) purposeful exercise ≤2 days per week for 30 min; (f) asymptomatic (i.e., no signs or symptoms of acute or uncontrolled cardiovascular, metabolic, or renal disease) based on the Get Active Questionnaire (70), (g) sufficient visual function to complete cognitive tasks (e.g., no scotomas) and (h) access to an internet-enabled device to participate in the intervention. Exclusion criteria are: (a) other neurological, medical or psychiatric condition that might impede cognition (e.g., traumatic brain injury, learning disability) excluding depression and anxiety; (b) current dementia; (c) substance use or dependence disorder; (d) hearing impairment that would interfere with the ability to effectively take part in the videoconference sessions.

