### Stage 4: Analysis and dissemination

Stage 4 involves *analysis and dissemination of results*. Data will first be compiled and analyzed using IBM SPSS Statistics (version 28). Descriptive statistics will be compiled to characterize the sample. Comparisons between baseline and follow-up on the outcome measures for all completers will be conducted using *t*-tests. The primary outcome measure is feasibility and will be evaluated according to the following: eligible participants excluded or not agreeing to participate, completion rate of assessments, attendance at intervention sessions, adherence to homework, attrition, and facilitator SOAP notes. The secondary outcome measure is CF performance on the PASAT. CF scores will be derived according to previously documented procedures (36). The intervention will be considered effective if at least a small effect size (i.e., improvement in CF) is observed between baseline and follow-up. Data from the structured interview will be analyzed quantitatively. Facilitator SOAP notes will be subjected to thematic analysis. Knowledge translation will involve traditional dissemination routes (i.e., journals, conferences) with the additional plan to disseminate this research among health care professionals by providing in-service presentations and hospital rounds. We will also seek to disseminate the findings to the lay public through community presentations, and educational materials. It is our intention to include trainees at all levels in this research to educate new health care professionals on the benefits of behavioural interventions on patient outcomes. We will also engage a Patient Advisory Committee to seek input on other possible avenues of communicating the results from this study to individuals in the MS community. We will follow CONSORT reporting guidelines for pilot feasibility trials (72).

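### Stage 4 judges improvement in cognitive fatigability by an observed small effect, the Discussion by statistical significance, and a sample sized for feasibility gives no basis for expecting significance

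*Protocol article*

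**What the plan says.** All statements are in the protocol article.

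- **Stage 4: Analysis and dissemination** gives the rule for CF: "The intervention will be considered effective if at least a small effect size (i.e., improvement in CF) is observed between baseline and follow-up". It attaches no significance requirement and no number to the word small. The same section describes the analysis: "Comparisons between baseline and follow-up on the outcome measures for all completers will be conducted using" t-tests. Feasibility is named there as the primary outcome and CF on the PASAT as the secondary one.
- **Discussion**, among the anticipated outcomes, says that those who complete the intervention "will demonstrate an improvement in CF as measured by a positive and statistically significant change documented from baseline assessments". The sentence just before it says that "past studies have demonstrated that having at least 12 completers is sufficient to yield the necessary outcomes in a pilot study".
- **Stage 3: Implementation of intervention** gives the sample size: "we will recruit a sample of 20 individuals with MS who meet the inclusion criteria", so that "we have 15 individuals in the final sample (allowing for 25% attrition" is provided for. The reason given is that "a minimum sample size of 12 to 15 is sufficient to determine feasibility of pilot studies in MS".

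The article states no significance level, sidedness, SD of change or power for CF.

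**The concern.** Both statements concern the same quantity, the change in CF from baseline to follow-up in completers. One asks only that the observed effect be at least small. The other says that improvement is measured by significance. In a sample of 12 to 15 these are far apart, so a mid-range result satisfies the Stage 4 rule and falls short of the Discussion's measure.

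The stake is what the pilot may claim about efficacy. The Materials and methods section and the Discussion both say that efficacy is tested on a smaller scale, and Stage 5 ties planning of the later randomized trial to the CF findings. Neither yardstick suits that purpose. Significance is unlikely with this sample unless the effect is large, and a bare point estimate above a small threshold can easily arise by chance.

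**Working it through.** **Inputs from the article.** 20 recruited; 25% attrition; 15 in the final sample; 12 completers accepted; t-tests of baseline against follow-up in completers. There is one arm, so the test is taken as paired.

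**Inputs assumed.** Two-sided 0.05 (one-sided 0.05 as sensitivity). Small is taken as a standardized mean change dz = 0.2, where dz is the mean change divided by the SD of change.

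**1. The article's own figure.** 20 × (1 − 0.25) = 15. It reproduces.

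**2. Smallest observed effect that is significant.** dz = t(0.975, n−1)/√n.

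- n = 15: 2.145/3.873 = 0.55
- n = 12: 2.201/3.464 = 0.64
- n = 20 (nobody lost): 0.47
- n = 15, one-sided 0.05: 0.45

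The n = 15 value is also the half-width of the 95% confidence interval for the mean change, in SD-of-change units.

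**3. Power if the true effect is only small.** Noncentral t with n−1 degrees of freedom and noncentrality dz·√n; at n = 15 this is 0.2 × 3.873 = 0.775.

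- n = 15: 11.2%; n = 12: 9.7%; n = 20: 13.6%
- n = 15, one-sided 0.05: 18.2%
- For 80% power at dz = 0.2: 199 pairs (156 one-sided)
- Effect detectable with 80% power: dz = 0.78 at n = 15, 0.89 at n = 12

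If small means 0.2 of the raw-score SD, then dz = 0.2/√(2(1−r)), where r is the correlation between baseline and follow-up. At r = 0.3, dz = 0.169 and power at n = 15 is 9%. At r = 0.5, dz = 0.2 and power is 11%. At r = 0.8, dz = 0.316 and power is 21%. At r = 0.9, dz = 0.447 and power is 36%.

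**4. How often the yardsticks part.** At n = 15, the chance that the observed dz is at least 0.20, minus the chance of a significant improvement (differences taken before rounding):

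| True dz | Observed dz ≥ 0.20 | Significant improvement | First but not second |
|---|---|---|---|
| 0 | 22.6% | 2.5% | 20.1% |
| 0.2 | 50.5% | 10.8% | 39.7% |
| 0.3 | 65.4% | 19.0% | 46.4% |
| 0.4 | 78.2% | 30.3% | 48.0% |
| 0.5 | 87.8% | 43.8% | 44.0% |
| 0.8 | 99.0% | 82.1% | 16.8% |

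**5. The Stage 4 rule when nothing has changed.** The first row of the table gives P(observed dz ≥ 0.20) = P(t with 14 df ≥ 0.775) = 22.6%.

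**The case against.** The strongest reply is that the article contains one rule and one forecast. The Stage 4 sentence is the rule. The Discussion sentence stands in a list of anticipated outcomes, and nothing makes significance a condition for calling the intervention effective or for going on to a larger trial. Any significant improvement at these sample sizes also meets the small-effect rule, so the two are not logically incompatible. The article never says that the true effect is expected to be small, so 11% is not the power of a hypothesis it commits to. Finally, the study was sized for feasibility and CF is secondary in Stage 4, so low power is no error in itself.

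Much of this stands, and it rules out stronger readings that a reader might infer:

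- *The yardsticks disagree over most plausible results.* At 15 pairs the chance of disagreement does not reach one half for any true effect examined; at 12 it peaks at about 51%. A majority appears only among results that already meet the small-effect rule: 79% of those are non-significant at a true dz of 0.2, and 50% at 0.5.
- *The authors may choose between two formal success criteria, or a non-significant result would stop the programme.* No such provision exists. The Abstract ties the decision on a randomized trial to feasibility outcomes.
- *The sample size is miscalculated.* It is not, and no power is claimed.

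What the reply does not remove is that the Discussion says how improvement is to be measured, in terms that differ from Stage 4, and that nothing in the sample-size reasoning supports expecting significance.

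**Conclusion.** The point holds as a minor-to-moderate matter of consistency, not as an arithmetic error. The expectation of significance has no support in a sample justified only by feasibility, and it uses a different measure of CF improvement from Stage 4. With 15 pairs the gap covers observed standardized changes from about 0.20 to 0.55, with a chance of about 17% to 48% of landing there for true effects of 0 to 0.8.

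The Stage 4 rule also cannot carry a claim of effectiveness on its own, because it would call an intervention with no true change effective in about 23% of such studies.

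All these figures rest on an assumed paired t-test and effect-size metric, and those involving significance also on an assumed level and sidedness. A statistical analysis plan that is not shown may fix them. The power figure is the most sensitive: about 11% in the base case, 18% one-sided, and 9% to 36% if small is scaled by the raw-score SD with correlations of 0.3 to 0.9. In every case examined, significance remains unlikely if the true effect is only small.

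**What to change.** In the Discussion, delete the words that require the change to be statistically significant. In both the Discussion and Stage 4, use one statement for CF, along these lines: the mean change from baseline to follow-up in completers will be reported with its 95% confidence interval and a standardized effect whose denominator is named (SD of change or baseline SD); with 15 pairs the interval has a half-width of about 0.55 SD of change; the result is preliminary, and the study is not powered to test efficacy. This statement replaces the Stage 4 sentence that declares the intervention effective on the point estimate alone.

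The cost is wording only. Sample size, assessments and data collection are unchanged. The price is a less favourable stated expectation.

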## Data Availability

The original contributions presented in the study are included in the article/Supplementary Material, further inquiries can be directed to the corresponding author/s.
